#### Two-month follow-up

Study staff will contact participants and schedule a follow-up appointment at the GP practice or carry out a home visit 2 months after randomisation. At this visit, the researcher will record information on the types of medication currently used, and any adverse events. S/he will collect information on smoking behaviour including self-reported smoking status, the number of cigarettes smoked per day, current pack/pouch size, use of e-cigarettes and pharmacotherapy (NRT, varenicline or bupropion) and nicotine dependence. A saliva sample and exhaled CO measurement will be taken by the researcher. S/he will also record whether the participant accessed any type of support (e.g. NHS SSS) for stopping or reducing smoking since randomisation. If the participant reports that they have stopped smoking and they are taking a particular medication that requires a dose adjustment due to this, the participant’s GP will be informed. For intervention group participants, we will assess the frequency of telephone support and use of the online video tutorial. If participants are unable to attend a practice visit or a home visit, information on smoking behaviour will be collected by telephone, text message or email. Salivettes will be posted out to participants with instructions on how to give a saliva sample and a pre-paid envelope will be provided for returning the sample back to the study team.

#### Eight-month follow-up

The study team will contact all participants 6 months after their 2-month follow-up by telephone, text message or email to establish smoking status, number of cigarettes smoked per day, current pack/pouch size, use of pharmacotherapy, use of e-cigarettes and any serious adverse events (SAEs). Participants who declare abstinence will be invited to return to the practice or receive a home visit by a member of the study team for exhaled CO measurement to confirm this. Every effort will be made to contact participants exactly 6 months after the 2-month follow-up, before data are classed as lost to follow-up. If the participant is unable to provide a CO measurement to validate abstinence, a salivette will be posted to the participant with instructions on how to return the sample back to the study team. Again, if the participant reports that they have stopped smoking and they are taking a particular medication that requires a dose adjustment, the participant’s GP will be informed.

### Treatments

#### Treatment arms

##### Control

Practitioners will deliver routine smoking cessation advice and treatment to all patients. Although usual care varies by practice, this typically involves standard brief advice about stopping smoking and assistance to do so either by referral to the NHS SSS or offer of pharmacotherapy. Some practices offer in-house SSS delivered by nurses or healthcare assistants trained to provide stop smoking support. In some practices, practitioners prescribe cessation medication. Pharmacotherapies provided as part of this support by the practitioner or through the SSS referral include either nicotine replacement therapy (used as single form or combination NRT), varenicline or bupropion. If the patient agrees to a referral to the SSS or accepts a prescription for pharmacotherapy, the GP/practice nurse will fill in a patient ineligibility card. Practitioners will only open the randomisation envelope if the patient declines usual care treatment. If the randomisation card reveals that the patient is allocated to the control arm, no further action will be necessary as the GP/practice nurse has delivered all components of usual care.

##### Intervention

Participants in the intervention group will have already received usual care by the GP or practice nurse as described above for the control group. If randomised to the intervention group, the GP or practice nurse will deliver brief advice about e-cigarettes. All practitioners will receive online training in how to deliver the advice and motivate patients to take up the offer of an e-cigarette. The GP/practice nurse will be encouraged to do the following during advice giving: describe the offer positively, establish the evidence-base for e-cigarettes, emphasise switching from smoking and alleviate any health concerns about the risks of vaping. Each practitioner will be given a prompt sheet as a reminder.

The GP/practice nurse will ask the participant whether s/he would be willing to try an e-cigarette, upon which the participant will be given an e-cigarette starter pack and an accompanying practical support booklet. The starter pack will contain three different flavoured bottles of e-liquid in two nicotine strengths (2 × 18 mg/ml and 1 × 12 mg/ml). Participants will need to purchase their own e-liquid thereafter. They will also receive an introductory call from an experienced vaper who will help with any technical queries they might have when first using the device. They will have the option to opt out of receiving this call.

At the end of the consultation, practitioners will record whether brief advice about e-cigarettes was given and whether the e-cigarette starter pack was accepted.

##### Practical support booklet, telephone support service and online tutorials

Intervention group participants will have access to three resources to promote patient self-efficacy, skills and positive outcome expectations about e-cigarettes, should they accept the offer of a starter pack. The first resource is a practical support booklet and will include the following: information on what is an e-cigarette, instructions on how to set up the device, how to refill and charge it, correct ways to vape, a list of local shops that sell e-liquids and common issues with use. The booklet will contain motivational support to reinforce practitioners’ advice about e-cigarettes, including the benefits of cutting down on cigarettes through e-cigarette use and addressing perceived risks and concerns about first use.

The second resource available to participants is telephone support. The practical support booklet will include the contact details of a dedicated team of experienced vapers who will operate the telephone support service. Although the vape team will have specialist knowledge on e-cigarette use, they will be trained in the study procedures and protocol for delivering technical support on e-cigarettes by staff at the University of Oxford. Each member of the vape team will be assigned 10–15 participants to assist. The study team will identify which participants accepted an e-cigarette starter pack, after the annual review appointment. If the participant accepted, his/her contact details will be passed on to a member of the vape team. The vape team will contact each participant to introduce themselves and offer any assistance on the set up and use of the e-cigarette device within one week of randomisation. Subsequently, participants will be able to contact the vape team through a telephone support service; they can leave a message for the vape team, who will return the call if they are unable to take the call immediately. All calls will be audio-recorded via a call-recording app on the study mobile phone with the consent of participants to monitor the advice provided by the vape team.

The practical support booklet will also include details of a study-dedicated website featuring a series of online video tutorials. The videos will include instructions on how to use the e-cigarette, demonstrations with a non-vaper and a testimonial from a vaper that switched from smoking to e-cigarettes.

### Practitioner training

The training will build on practitioner motivation, skills, self-efficacy and positive outcome expectancies for encouraging adherence to the protocol and delivery of the intervention [54]. LifeGuide, an open source software platform, will be used to develop and deliver the training online [57]. LifeGuide will allow us to control all aspects of the design, making changes where necessary during development and allow us to evaluate the usability and acceptability of the training.

We will draw on quantitative research to collate the evidence-base on the use of e-cigarettes for harm reduction, its use as a cessation aid and its safety profile to form part of the educational component of the training. This information—derived from sources such as the systematic review on e-cigarettes for reduction and cessation [39] and the Public Health England (PHE) evidence update [50]—will be used to develop a set of ‘key facts’ on the benefits of cutting down in smokers with chronic diseases. We will address practitioners’ main concerns about e-cigarettes, which have been reported elsewhere [48]. We will also draw on existing training resources offered to stop smoking practitioners from the National Centre for Smoking Cessation Training website. We will convey what is known and unknown about e-cigarettes and their place in treating smokers with no desire to quit. This will be followed by training to use a few key evidence-based behavioural methods from the behaviour change technique (BCT) taxonomy [58] (e.g. problem solving, instruction on how to perform a behaviour, verbal persuasion to boost self-efficacy) that practitioners will use to motivate hardcore smokers in the intervention group to try e-cigarettes if they decline help to stop smoking. This section will include video role-play scenarios between GPs and actors to show the skills in action in different settings. We will explain how important it is to trial integrity not to contaminate the study by offering e-cigarettes and advice to the control group. The training will outline the difference between what constitutes the standard care for the control group and the procedure to follow in the intervention group.

Practitioners will be given login details to access the training before the start of the intervention period. The study team will check that the training has been carried out and completed prior to delivery. If there is any uncertainty about the content and procedure, practitioners will be able to contact the study team for clarification.

### Embedded qualitative study

Participants in the intervention group will be asked whether they would be willing to participate in a telephone interview after the 2-month follow-up visit. We will purposively select up to 40 participants who took up the offer and tried an e-cigarette, those who reduced and/or quit and those who refused to use them. A semi-structured interview guide will be used to assess patients’ knowledge of e-cigarettes, their experiences of use and the degree to which the information provided by their practitioner made a difference to them and their smoking behaviour. Additionally, we will explore patients’ views on acceptability and appropriateness of being given advice and an offer of an e-cigarette by their practitioner.

We will conduct telephone interviews with up to 20 practitioners after they have seen their last enrolled patient to assess what worked well, any challenges faced when delivering the intervention and the appropriateness of the training received. We will also approach members of the vape team after they have completed their involvement in the study on what worked well and any challenges faced in providing technical support to participants in the trial. All interviews with patients, practitioners and the vape team will be audio-recorded and transcribed.

### Trial outcome measures

#### Primary outcomes

The first primary outcome is 7-day point-prevalence abstinence from smoked tobacco at 2 months. Abstinence is defined as complete self-reported abstinence from smoking—not even a puff—in the past 7 days, accompanied by a salivary anabasine concentration of < 1 ng/ml. If there are technical issues with the analysis of saliva samples (e.g. if there is not enough saliva present in the sample for anabasine analysis), we will use exhaled CO as verification of abstinence (CO < 10 ppm).

The second primary outcome is reduction in cigarette consumption at 2 months. Reduction is defined as a 50% reduction in self-reported cigarettes per day on each of the last 7 days at 2 months compared with baseline consumption, accompanied by evidence of reduced smoke intake indicated by salivary anabasine concentrations lower than baseline.

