### Inclusion criteria

Participant is willing and able to give informed consent for participation in the studyAged 18 years or aboveCurrent smoker with a value of at least 10 parts per million (ppm) for exhaled carbon monoxide (CO) and smokes a minimum of eight cigarettes/8 g of tobacco per day (including pipe, cigars or tobacco roll-ups)Diagnosed with one or more of the following chronic conditions: ischaemic heart disease, peripheral vascular disease, hypertension, diabetes mellitus (type 1 and type 2), stroke, asthma, COPD, chronic kidney disease, depression, schizophrenia, bipolar disorder or other psychoses

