#### Baseline visit

The baseline visit will take place in the patient’s GP practice. The researcher will assess the patient’s eligibility and obtain written informed consent (Additional file 5). The researcher will check for eligibility based on the patient’s medical history, medication use, current e-cigarette use and smoking status, which will be biochemically verified through exhaled carbon monoxide (CO) readings. Medical history and medication use may be checked against the participant’s primary care records to ensure accuracy and completeness. The researcher will also collect basic demographic data, information on smoking history and a saliva sample. Table 1 outlines the data that will be collected at baseline.

**Table 1 Tab1:** Data collection at baseline visit

Demographics	Basic demographic information
Medical history	Medical problems and concomitant medication
Smoking history	Information on smoking and quitting history (age when started smoking, number of cigarettes smoked per day, when the last cigarette was smoked, type of cigarettes smoked per day (roll-ups or factory-made), usual pack/pouch size, nicotine dependence, motivation to stop smoking, self-efficacy and outcome expectancies, history of any pharmacotherapy or e-cigarette use and exhaled CO measurement)
Biological samples	Saliva samples to measure anabasine (for smoke intake) and cotinine (for nicotine intake)

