### Analysis plan

#### Primary and secondary analyses

The proportion of participants who reduce smoking in each group will be presented. A log-binomial regression model will be applied to the data and the treatment effect will be reported as a relative risk and 95% confidence interval, adjusted for GP practice. A similar procedure will be used to analyse the proportion of participants who abstain from smoking. Analyses will be carried out on an intention-to-treat basis, according to the Russell Standard [60], where participants lost-to-follow up are assumed to be smokers or not to have reduced and we will impute missing anabasine concentrations with the baseline value.

The mean (SD) change in salivary anabasine from baseline to 2 months will be reported for each group and the difference and 95% CI will be computed using linear regression with adjustment for GP practice. Assumptions of linear regression will be assessed and if violated a Mann-Whitney test will be adopted and the median (IQR) will be used to summarise the data and difference in medians (95% CI) will be reported.

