#### Sample handling

Researchers will obtain saliva samples from participants at baseline and 2-month follow-up visits to measure salivary cotinine and anabasine concentrations. Cotinine, a major metabolite of nicotine, has a half-life of approximately 20 h in smokers [67] and is stable at room temperature for up to 12 days [68]. Anabasine, a specific biomarker of tobacco smoke, has a half-life of 16 h [69] and is also stable at room temperature for up to 14 days.

Saliva will be collected in a plastic vial containing a sterile dental roll (Salivette, Sarstedt). The container will be labelled with the patient ID, type of sample, collection date and time, then transported back to the university. Samples will be sent to the laboratory as soon as they are collected, or they may be stored for up to 7 days at room temperature until they are shipped in batches to a laboratory. The laboratory will store and freeze the samples at − 20 °C until there is a sufficient batch for processing. Salivary cotinine and anabasine concentrations will be determined by liquid chromatography-tandem mass spectrometry (LC-MS/MS) assay. If insufficient saliva is available in the sample for both cotinine and anabasine analysis, anabasine will take priority in the assay. All samples will be disposed of by laboratory staff after final analysis.

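### Carrying baseline anabasine forward can verify abstinence without a 2-month sample when the baseline value is already below 1 ng/ml

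*Protocol article*

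**What the plan says.** All references are to the protocol article.

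- **Entry.** Inclusion criteria require exhaled CO of at least 10 ppm and at least eight cigarettes or 8 g of tobacco a day. At the Baseline visit the researcher checks "smoking status, which will be biochemically verified through exhaled carbon monoxide (CO) readings". Saliva is collected there too, but no anabasine level is required. Under Sample handling, "The laboratory will store and freeze the samples at − 20 °C until there is a sufficient batch for processing", so the result cannot be relied on as known at entry.
- **Abstinence at 2 months (Primary outcomes).** Two conditions apply: "complete self-reported abstinence from smoking—not even a puff—in the past 7 days", and this must be "accompanied by a salivary anabasine concentration of < 1 ng/ml". The cut-off is absolute and makes no reference to the participant's own baseline.
- **CO fallback (Primary outcomes).** "If there are technical issues with the analysis of saliva samples", CO below 10 ppm is used instead.
- **Reduction (Primary outcomes).** The biochemical condition is relative: anabasine must be below the participant's own baseline.
- **Missing data (Primary and secondary analyses).** People lost to follow-up count as smokers and as not reduced, and "we will impute missing anabasine concentrations with the baseline value".
- **Non-attendance (Withdrawal criteria).** Those who miss follow-up visits count as smoking and not reduced.
- **Remote data (Two-month follow-up).** Someone who cannot be seen in person may give smoking data by phone, text or email, and a saliva kit is posted. A self-report can therefore exist with neither a sample nor a CO reading.

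**The concern.** One imputation rule serves two checks that work differently. For reduction, a carried-forward baseline value can never be lower than itself, so a missing sample always fails. For abstinence, it fails only if the baseline value was at least 1 ng/ml. Below that, the missing sample turns into a pass, supplied by a measurement taken while the person was a confirmed smoker.

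Biochemical confirmation is part of the definition of a primary outcome, and its purpose is to guard against over-reporting. Participants know whether they were offered an e-cigarette, so over-reporting could differ between arms. The same 2-month anabasine check also feeds 6-month prolonged abstinence, although that outcome has a further check at 8 months.

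**Working it through.** **1. The plan's own figure.** Two-sided comparison of two proportions, pooled variance, 160 per arm:

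- Reduction, 8% v 8% × 2.8 = 22.4%, alpha 0.025: power 91.5%.
- Stopping, 5% v 5% × 3.4 = 17%, alpha 0.05: power 93.3% uncorrected. With continuity correction, 158 per arm (316 in total) gives 90%.

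The stated total of 320 is reproduced and is not in dispute.

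**2. The rules side by side, for abstinence.**

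| Situation at 2 months | Baseline ≥ 1 ng/ml | Baseline < 1 ng/ml |
|---|---|---|
| No contact | smoker | smoker |
| Sample taken but cannot be analysed | decided by CO | decided by CO |
| Reports abstinence remotely, kit not returned, baseline imputed | check fails | **check passes** |
| Same, if the non-attendance rule takes precedence | smoker | smoker |
| Reports abstinence, measured value unchanged from baseline | check fails | check passes |

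The third row is the defect. The fourth shows that it disappears under one reading of the article. The last row is a separate matter: the value is really measured, but it does not discriminate for that person.

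**3. Size of the imputation route.** The article gives none of these inputs, so all are assumptions:

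- m, share giving a self-report without a sample: 5% to 30%
- f, share below 1 ng/ml at baseline: 5% to 20%
- u, share of those who wrongly report abstinence: 5% to 20%

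Expected false passes in the trial = 320 × m × f × u.

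- Low: 320 × 0.05 × 0.05 × 0.05 = 0.04
- Middle: 320 × 0.10 × 0.10 × 0.10 = 0.32
- High: 320 × 0.30 × 0.20 × 0.20 = 3.84

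The high end is generous. If the expected 70% follow-up means giving 2-month data, m = 30% would be 30/70 = 43% of those followed up.

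**4. Direction.** The planned events are 160 × 0.05 = 8 (control) and 160 × 0.17 = 27.2 (intervention). Half of the totals above fall in each arm: 0.02, 0.16 and 1.92.

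| False passes | Low | Middle | High |
|---|---|---|---|
| Both arms, true RR 3.4: (27.2 + e)/(8 + e) | 3.39 | 3.35 | 2.94 |
| Control arm only, true RR 3.4: 27.2/(8 + e) | 3.39 | 3.33 | 2.74 |
| Intervention arm only, true RR 1: (8 + e)/8 | 1.00 | 1.02 | 1.24 |

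**5. The last row of the table in step 2, for scale.** If a share f is below the cut-off and a share s of continuing smokers in both arms reports abstinence, each observed rate is p + (1 − p) × f × s.

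- f = 5%, s = 10%: 5.48% v 17.42%, RR 3.18, power 92.2% (from 93.3%).
- f = 10%, s = 20%: 6.90% v 18.66%, RR 2.70, power 88.7%.

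If f is zero, neither route has any effect.

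**The case against.** The strongest reply is that the perverse case needs four things at once: a baseline below 1 ng/ml, a false report of abstinence, no returned kit and no CO. Entrants smoke at least eight cigarettes or 8 g of tobacco a day and have CO of at least 10 ppm, and the article describes anabasine as specific to tobacco smoke with a 16-hour half-life. Nothing in it suggests that many would be below the cut-off. The non-attendance rule, read strictly, closes the route. Carrying baseline forward also has an evident purpose: it fails the reduction check and gives zero change in the mean-change analysis. A separate analysis plan may settle the matter.

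Most of this stands and limits the point. What remains is that the article does state the imputation rule, places it in the same sentence as the handling of the binary outcomes, and does not say whether the non-attendance rule overrides remotely supplied data.

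A reader might infer more than the text supports:

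- *That any unusable sample becomes a pass.* It does not. Samples that cannot be analysed go to CO. Only a sample never returned is not plainly covered.
- *That the plan reverses its principle that missing means smoking.* It does not. People lost to follow-up still count as smokers, and the imputation is conservative for everyone at or above 1 ng/ml at baseline.
- *That the rule favours the intervention.* That needs over-reporting concentrated in that arm. Participants know what they were offered but are not told that e-cigarettes are the subject of the study, and equal misreporting pulls the risk ratio towards 1.
- *That the absolute cut-off or the CO-based entry is itself an error.* Both are legitimate design choices.

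**Conclusion.** The point holds in a narrow form. As written, the imputation rule can let a value measured while smoking verify abstinence for a remote self-reporter who was below 1 ng/ml at baseline and returned no sample, unless the non-attendance rule takes precedence. Self-reported abstinence is still required, so the gap removes a check and does not by itself create an abstainer.

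The logic rests on the text alone; the size does not. With the share below 1 ng/ml undocumented and possibly zero, the imputation route gives roughly 0.04 to 3.8 false passes in 320 over the assumed ranges, in either direction. This is a minor correction to a stated rule and no threat to the trial's conclusions as the documents stand.

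**What to change.** 1. In Primary and secondary analyses, limit baseline imputation of anabasine to the reduction check and the mean-change analysis. State that an imputed value never verifies abstinence, so that self-reported abstinence without a measured 2-month anabasine, or the CO fallback, counts as smoking.
2. Reconcile this with Withdrawal criteria and Two-month follow-up, so that it is clear how remotely supplied data are scored when no visit takes place.
3. Report by arm the number with baseline anabasine below 1 ng/ml. If it is zero, the matter is closed.
4. As a sensitivity analysis, require 2-month CO below 10 ppm as well for those participants. Everyone entered at 10 ppm or more, so passing this always marks a change since entry. It is better as a sensitivity analysis than as a new primary definition, because switching markers for a subgroup is debatable.

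The cost is a few sentences and one table row. Baseline anabasine and CO at the 2-month visit are already collected, and the article places the trial in follow-up, so the wording can be settled before analysis. The downside is that a few remote responders who did stop but returned no sample count as smokers. In the sensitivity analysis, participants below the cut-off who have no CO reading would also fail.

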#### Secondary outcomes

Secondary outcome measures for abstinence include 7-day point prevalence abstinence measured at 8 months, biochemically confirmed by an exhaled CO of < 10 ppm. We will also measure 6-month prolonged abstinence using the Russell standard criteria, defined as smoking fewer than five cigarettes between 2- and 8-month follow-ups, confirmed by an anabasine concentration of < 1 ng/ml at 2 months and an exhaled CO concentration of < 10 ppm at 8 months (or anabasine concentration of < 1 ng/ml at 8 months if CO measurement unavailable). There is no funding for analysing all saliva samples at 8 months; therefore, we will verify abstinence using exhaled CO in the first instance.

As an additional measure of smoking reduction, we will assess the mean change in salivary anabasine concentrations from baseline to 2 months.

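### A quitter verified by CO because the 2-month saliva sample failed is scored as a non-reducer and also fails prolonged abstinence

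*Protocol article*

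**What the plan says.** All references are to the Protocol article.

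- **Abstinence at 2 months (Primary outcomes).** Self-reported 7-day abstinence "accompanied by a salivary anabasine concentration of < 1 ng/ml". If the saliva cannot be analysed, for example because there is too little of it, "we will use exhaled CO as verification of abstinence (CO < 10 ppm").
- **Reduction at 2 months (Primary outcomes).** A 50% fall in self-reported daily cigarettes, "accompanied by evidence of reduced smoke intake indicated by salivary anabasine concentrations lower than baseline". No substitute marker is given.
- **Prolonged abstinence (Secondary outcomes).** Fewer than five cigarettes between the two follow-ups, "confirmed by an anabasine concentration of < 1 ng/ml at 2 months and an exhaled CO concentration of < 10 ppm at 8 months". The only substitution is at the later visit: "or anabasine concentration of < 1 ng/ml at 8 months if CO measurement unavailable".
- **Missing values (Primary and secondary analyses).** After stating that those lost to follow-up count as smokers or non-reducers, the same sentence adds that "we will impute missing anabasine concentrations with the baseline value".
- **Data available (Two-month follow-up).** At a visit in person, "A saliva sample and exhaled CO measurement will be taken by the researcher". Participants followed remotely post back saliva and give no CO reading.

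**The concern.** The plan foresees a failed saliva assay and deals with it for one primary outcome only. Abstinence is the extreme case of reduction, so anyone who meets the first should meet the second. If the definitions are followed exactly, a verified quitter can be recorded as someone who did not cut down, and cannot later be recorded as a prolonged abstainer.

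Both primary outcomes enter the Holm-Bonferroni procedure, and the planned event counts are low. If the scoring is settled only when such cases turn up in the data, it becomes a choice made after the data are seen.

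**Working it through.** **1. One participant, scored by each rule.** Take someone who attends at 2 months, reports no smoking for 7 days, has CO < 10 ppm, and whose saliva cannot be assayed.

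| Outcome | Rule applied | Result |
|---|---|---|
| Abstinence, 2 months | CO fallback | Success |
| Reduction, 2 months | Imputed anabasine = baseline, so not lower than baseline | Failure |
| Reduction, 2 months | No imputation, so no value to test | Failure |
| Prolonged abstinence | No 2-month anabasine < 1 ng/ml | Failure, whatever happens up to 8 months |
| Abstinence, 2 months, if imputation is applied to it as well | Anabasine = baseline value | Failure, if baseline is ≥ 1 ng/ml |

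The reduction result is certain, because it does not depend on how the imputation clause is read. The prolonged-abstinence result follows from the definition as written. The last row is only one possible reading. It also assumes a baseline anabasine of at least 1 ng/ml, which the article does not state but which is likely, since entry required CO of at least 10 ppm and at least eight cigarettes (or 8 g of tobacco) a day.

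**2. The plan's own sample size.** Inputs from Sample size and Participant entry: 160 per arm; control rates 5% (stopping) and 8% (reducing); risk ratios 3.4 and 2.8; power 90%; alpha 0.025, then 0.05 (taken as two-sided). The intervention rates are 0.05 × 3.4 = 17% and 0.08 × 2.8 = 22.4%. With the pooled normal approximation,

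power = Φ{ [ |p1 − p0|√n − z(1−α/2)·√(2p̄(1 − p̄)) ] / √(p0(1 − p0) + p1(1 − p1)) }, where p̄ = (p0 + p1)/2.

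- Reduction, alpha 0.025: [0.144 × 12.649 − 2.241 × 0.508] / 0.497 = 1.37, power 91.5%.
- Abstinence, alpha 0.05: [0.12 × 12.649 − 1.960 × 0.442] / 0.434 = 1.50, power 93.3%.

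The stated 320 is consistent with its inputs and is not in dispute.

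**3. How many people.** The article gives no assay failure rate, so 5–15% is assumed.

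- Intervention: 160 × 0.17 = 27.2 abstainers; × 0.05 to 0.15 = 1.4 to 4.1.
- Control: 160 × 0.05 = 8 abstainers; × 0.05 to 0.15 = 0.4 to 1.2.

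**4. Effect on the reduction outcome.** Treat all abstainers as a subset of reducers, and let a fraction f of abstainers in both arms be scored as non-reducers. The rates become 0.08 − 0.05f and 0.224 − 0.17f. The 20% row is a stress case beyond the assumed range.

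| f | Control | Intervention | Risk ratio | Power at 0.025 |
|---|---|---|---|---|
| 0 | 8.00% | 22.40% | 2.80 | 91.5% |
| 5% | 7.75% | 21.55% | 2.78 | 89.9% |
| 10% | 7.50% | 20.70% | 2.76 | 87.9% |
| 20% | 7.00% | 19.00% | 2.71 | 83.3% |

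Reducers who still smoke and have no usable sample also fail. If 10% of all reducers are lost in both arms, the rates are 0.08 × 0.9 = 7.2% and 0.224 × 0.9 = 20.2%, the risk ratio stays at 2.8, and power is 87.5%.

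**5. If imputation did override CO for abstinence.** Losing 5%, 10% or 20% of abstainers equally in both arms leaves the risk ratio at 3.4 and lowers power at alpha 0.05 from 93.3% to 91.9%, 90.2% or 86.1%.

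**The case against.** The strongest reply is that this is a condensed article, that scoring rules for unusable samples usually sit in the full protocol or analysis plan, and that few people are involved. The laboratory section also gives anabasine priority over cotinine when saliva is short, which lowers the number of failed assays. The last two points stand and limit the size. The first does not dispose of the matter. The article does more than stay silent: it fixes a fallback for one primary outcome, fixes a definition without one for the other, and fixes an imputation that cannot satisfy that definition.

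Three stronger readings are tempting, and the article does not support them.

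- **That the CO rule and the imputation rule flatly contradict each other for abstinence.** The imputation clause closes a sentence about loss to follow-up and may be meant for those cases. The CO rule is the more specific one and would have no function if imputation overrode it. Precedence is not stated, so this is an ambiguity and no more.
- **That 8-month 7-day abstinence has a matching gap because its definition names only CO.** The Eight-month follow-up section provides for posting a saliva kit to anyone who declares abstinence but cannot give a CO reading, and Secondary outcomes describes CO as the first choice of verification. That largely answers the point. Nor is a prolonged abstainer who is not 7-day abstinent a contradiction in itself, since the prolonged definition tolerates up to four cigarettes.
- **That the trial result is biased because more successes are lost in the arm with more quitters.** More people are lost there in number, but with equal failure rates the risk ratio hardly moves.

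**Conclusion.** Wrong as written, minor in severity. Followed exactly, the definitions make a CO-verified quitter a non-reducer and exclude that person from prolonged abstinence. Whether imputation also disturbs the abstinence outcome is unclear and should be settled in the text.

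The number affected is unknown and probably small: about 1–4 intervention and 0–1 control abstainers at the planned event rates, if 5–15% of samples fail. The consequence is primary outcomes that disagree about the same person and a modest loss of power for reduction (91.5% to 89.9% at 5% failure, 87.9% at 10%). There is no material bias in the risk ratio as long as failure rates are equal between arms. The failure rate, its equality between arms, and abstainers being a subset of reducers are assumptions.

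**What to change.** Add three statements to the outcome definitions and the analysis plan:

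- (a) Anyone who meets the 2-month abstinence outcome, by anabasine or by the CO fallback, also meets the reduction outcome.
- (b) CO < 10 ppm at 2 months, used as the fallback, also satisfies the 2-month part of prolonged abstinence.
- (c) For the binary abstinence outcome, imputing the baseline anabasine does not override CO verification. The imputation still applies to the mean change in anabasine, so that this outcome keeps a value for everyone.

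Flag the cases that rest on CO and repeat the analysis without them.

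The cost is wording and one sensitivity analysis. No new data are needed, because CO is already measured at 2-month visits in person. The article reports the trial as in follow-up, so the rule can be fixed before database lock. Two limits remain. Participants followed remotely have no CO reading and are not helped. Reducers who still smoke and have no usable sample still count as failures; whether another marker should stand in for them is a separate choice that this fix leaves open.
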